## Abstract

**Background:**

Medical students are frequently affected by poor sleep quality. Since poor sleep quality has negative physiological and psychological consequences such as on executive function, there is an opportunity to improve sleep quality and executive functions using non-pharmacological intervention such as cognitive behavioural therapy.

**Objective:**

The aim of this study therefore is to determine if improving sleep quality could improve executive functions in medical students with poor sleep quality by comparing cognitive behavioural therapy for insomnia (CBT-I) with sleep hygiene education (SHE) in a randomized controlled trial (RCT).

**Methods:**

A parallel group, RCT with a target sample of 120 medical students recruited from government-based medical universities in Malaysia. Eligible participants will be randomized to internet group CBT-I or internet group SHE in a 1:1 ratio. Assessments will be performed at baseline, post-intervention, 1 month, 3-months, and 6-months. The primary outcome is between-group differences in sleep quality and executive function post-baseline. The secondary outcomes include pre-sleep worry, attitude about sleep, sleep hygiene and sleep parameters.

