## Methods

### Trial Design

A 2-arm, parallel-group RCT will be conducted, comparing ICBT-I with internet-delivered SHE (ISHE). The trial design is summarized in Figure 2. The study population will consist of preclinical medical students who meet the established criteria for poor SQ, as indicated by self-report assessments, which are internationally recognized as standardized instruments. The medical students will be randomly assigned in a 1:1 ratio to either the ISHE or ICBT-I group. All interventions will be conducted online using a paid Zoom (Zoom Video Communications/Qumu Corporation) platform. As shown in Figure 2, participants will receive an electronic document containing the participant information statement, screening instruments, informed consent form, and randomized allocation to the intervention groups. Both baseline and follow-up assessments will be conducted either online or via mobile platforms. Participants will be able to print the participant information statement, and contact details (phone numbers and emails) will be provided for participants to reach the researchers before consenting and during the data collection process.

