Module 5	Cognitive restructuring: identifying, reexamining, and modifying dysfunctional thoughts and beliefs about sleep and the consequences of poor sleep quality.	Stress management and sleep.
Module 6	Relapse prevention: actions to be taken to prevent poor sleep quality or relapse in sleep perturbations, including when it is appropriate to seek medical assistance and identify the conditions of safe pharmacotherapy.	Treatment evaluation and maintenance.

^a^ICBT-I: internet-based cognitive behavioral therapy for insomnia.

^b^ISHE: internet-delivered sleep hygiene education.

^c^PMR: progressive muscle relaxation.

The program includes a sleep diary in which medical students record their wake time, bedtime, sleep latency, night awakenings, and TST. Graphs will be generated based on the data entered by participants into the sleep diary. Additionally, various exercises will be included to ensure participants practice what they have learned. Participants will have the opportunity to repeat, internalize, and apply the modules, exercises, and examples to their daily lives at their own pace. Behavioral instructions will be provided to guide participants in completing the instruments, sleep diary, and responses during the program’s interactive phase.

Based on the preferred wake-up time and the average TST from the previous week, a sleep window will be proposed. To avoid excessive tiredness, a more flexible minimum time in bed of 6 hours has been chosen for this study. Participants are encouraged to extend their sleep window gradually. Once the sleep diary indicates an SE of 85% or greater over the past week, participants will be advised to add 15 minutes to their sleep window. However, if the recommended SE of 85% is not achieved, participants will be advised to reduce their sleep window based on their preferred average total sleep and wake-up times during the observation period. For those with an SE between 80% and 85%, the sleep window will remain unchanged, but it can be extended by 15 minutes if the efficiency is lower than 85%.

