Besides the overall recommendations on sleep hygiene, the medical students will be encouraged to focus on specific behaviors that received the highest scores in the Sleep Hygiene Index (SHI; ie, reducing coffee or alcohol consumption just before bedtime if the participant reports frequent use). They will also be guided by the Dysfunctional Beliefs and Attitudes About Sleep-16 (DBAS-16), particularly for participants who score highly on the item “feel irritable, depressed, or anxious during the day, mostly because I did not sleep well the night before.” This reflects a strong belief in the negative impacts of poor SQ. Such participants will be advised to explore whether there are any underlying reasons for their anxiety and depression, aside from insomnia.

The internet program will serve as the primary medium for delivering all intervention materials, with participants engaging with the materials independently. They will also have the opportunity to consult a clinical psychologist (see the “Withdrawal and Crisis Management Procedure” section). Additionally, participants are strongly encouraged to use the feedback form to contact a specialist, particularly if they are newly recruited into the RCT, experiencing negative effects from the ICBT-I or ISHE interventions, or encountering methodological or technical difficulties with the program. The content of the intervention is entirely based on the well-established ICBT-I, which has been validated and tested in previous studies [37].

Each module will be completed with a homework report, which participants will fill out and submit to their therapists. The therapist will review the report, worksheets, and sleep diary data. Written feedback will be provided within 48 hours, and the therapist will grant the medical student access to the subsequent module. Meanwhile, if the participant is inactive for 1 week, the therapist will be alerted via a mobile phone SMS text message, serving as a reminder and encouragement. If necessary, another SMS text message will be sent, followed by emails, with phone calls as the final step. The therapist (FM) in this study is a licensed clinical psychologist with expertise in poor SQ and insomnia-related CBT.

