### Monitoring of Intervention and Follow-Up Assessment

The flowchart for the research activities is summarized in Figure 2. An SMS text message reminder will be sent by the Zoom administrator 1 day prior to and 30 minutes before the intervention. Follow-up assessments will be conducted at 1-month, 3-month, and 6-month intervals after the postintervention to reassess participants’ SQ, executive functioning, self-reported sleep problems, SE, sleep cognition, and presleep arousal. The same instruments described in the previous section will be used for the assessments. All participants will be monitored for adherence to the intervention, and potential dropouts will be identified and addressed accordingly.

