### Data Analysis

Data will be analyzed using SPSS version 29 (IBM Corp.). Descriptive statistics will be used to obtain information on dropout rates, recruitment, and completeness. All participants will be included in the intention-to-treat analysis for assessing the main efficacy of the intervention, with no planned interim analysis for efficacy or futility. The baseline characteristics of participants will be presented according to their randomized group, with no inferential statistical tests performed at this stage.

For the RCT design, outcome measures will be assessed for normality and presented as either means with SD or medians with IQR, depending on the data distribution. Participants’ characteristics will be summarized using descriptive statistics, with categorical data presented as frequencies and percentages, and continuous data presented as means (SD) or medians (IQR). Normality will be tested using the Kolmogorov-Smirnov and Shapiro-Wilk tests.

Changes in all outcome measures (ie, SOL, TST, NOA, WASO, SQ, SE, dysfunctional beliefs about sleep, presleep arousal, and SHI) from pretreatment (T0) to the first (T1), second (T2), and third (T3) time points will be assessed for treatment effects using repeated measures analysis of variance. Both treatment and time interaction effects will be examined. Paired samples *t* tests will then be conducted within each condition to evaluate possible simple or main effects. Significant findings and statistical trends will be further analyzed using Cohen *d* effect size, which accounts for the correlation between pre- and posttreatment values.

Potential confounding factors, particularly class year and gender, will be addressed and analyzed as variables that may influence the research outcomes. These factors will be incorporated into the analysis through both univariate and multivariate linear regression analyses, allowing for the isolation of each factor and its association with the outcomes of interest.

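### Delivery is described both as group programmes on Zoom and as independent, self-paced use; the planned ANOVA treats students as independent, which is right only under the second description

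*Protocol article*

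**What the plan says.** Several places point to timed, and possibly shared, delivery:

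- Abstract, Methods: "Eligible participants will be randomized to internet group CBT-I or internet group SHE in a 1:1 ratio".
- Trial Design: "All interventions will be conducted online using a paid Zoom (Zoom Video Communications/Qumu Corporation) platform". Study Location likewise places the initial assessment and the experiment on Zoom.
- Monitoring of Intervention and Follow-Up Assessment: "An SMS text message reminder will be sent by the Zoom administrator 1 day prior to and 30 minutes before the intervention".

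Planned Interventions, under The Internet Group (CBT-I), points to individual delivery:

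- "The internet program will serve as the primary medium for delivering all intervention materials, with participants engaging with the materials independently".
- Participants can "apply the modules, exercises, and examples to their daily lives at their own pace".
- Once a student's homework has been reviewed, "the therapist will grant the medical student access to the subsequent module".

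On analysis, Data Analysis says that changes in the outcomes "will be assessed for treatment effects using repeated measures analysis of variance", from T0 to T3. Paired t tests follow, and regressions bring in class year and gender. No session-group term is named. Sample Size Estimation uses the same type of ANOVA (within-between interaction) with no design effect. The article gives no session size, number of session groups or rule for forming them.

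**The concern.** A reminder 30 minutes beforehand makes sense only for something with a start time, and the Abstract calls both programmes group programmes. Self-paced modules, released one student at a time, have no common start time. A reader cannot tell from the article whether students are treated together.

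This matters because the repeated measures ANOVA takes students within an arm as independent. If students attend in session groups, those in the same group share that group's experience and their outcomes may be correlated. The ANOVA standard errors would then be too small, and chance differences between a few session groups could be read as a benefit of ICBT-I. If each student works alone, the stated model has no such problem.

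**Working it through.** **The plan's own figure.** Sample Size Estimation gives alpha 0.05, power 95%, effect size f = 0.20, correlation 0.5 and 56 per group. For this interaction test the noncentrality is λ = f² × N × m / (1 − ρ), with df1 = m − 1 and df2 = (N − 2)(m − 1). The number of measurements m is not in the text, so it is assumed here. With m = 4 and N = 56 in total, λ = 0.04 × 56 × 4 / 0.5 = 17.92 on 3 and 162 df, and power is 95.4%. The inputs therefore reproduce 56 as a total, not per group. For m = 2, 3 and 5 the totals are 84, 66 and 48. That mismatch is a separate matter: it makes the trial larger than its inputs require and does nothing for the type I error. What counts here is that no clustering term enters the formula.

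**Error rate if sessions are shared and ignored.** Let g be the number of students per session group.

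- Design effect: DE = 1 + (g − 1) × ICC.
- Actual two-sided error at nominal 5%: 2 × [1 − Φ(1.96 / √DE)].

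Both g and ICC are assumptions. The ICC of 0.2 in Data Analysis belongs to a mediation example with repeated measures and is not a session ICC.

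Worked case, g = 10 and ICC 0.05: DE = 1 + 9 × 0.05 = 1.45; 1.96 / √1.45 = 1.63; error 10.4%. Then 120 / 1.45 ≈ 83, so 120 students carry the information of about 83.

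The formula was checked by simulating the ANOVA interaction with 60 per arm, correlation 0.5, no arm effect, a session effect in both arms at every post-baseline visit, and 3,000 runs per setting.

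| g | ICC | DE | Formula | Simulated, 4 visits | Simulated, 5 visits |
|---|---|---|---|---|---|
| any | 0 | 1.00 | 5.0% | 4.6% | 4.7% |
| 6 | 0.02 | 1.10 | 6.2% | – | – |
| 6 | 0.05 | 1.25 | 8.0% | 7.7% | 7.8% |
| 10 | 0.02 | 1.18 | 7.1% | 6.2% | 7.1% |
| 10 | 0.05 | 1.45 | 10.4% | 10.0% | 9.7% |
| 10 | 0.10 | 1.90 | 15.5% | 15.5% | 15.4% |
| 20 | 0.02 | 1.38 | 9.5% | 9.6% | 9.4% |
| 20 | 0.05 | 1.95 | 16.0% | 15.6% | 15.4% |

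A separate simulation with 1,500 runs per setting agrees within simulation error: 5.1% at g = 6, ICC 0.02; 8.1% at g = 6, ICC 0.05; 11.0% at g = 10, ICC 0.05; 14.8% at g = 10, ICC 0.10.

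**When the rate doubles.** An error of 10% needs 1.96 / √DE = 1.645, so DE = (1.96 / 1.645)² ≈ 1.42, that is (g − 1) × ICC ≈ 0.42. The ICC would have to exceed 0.084 at g = 6, 0.047 at g = 10 and 0.022 at g = 20.

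**The case against.** The strongest reply is that the detailed intervention text favours individual delivery. Content comes by video, sleep windows are set from each student's own diary, homework feedback is individual, and a student inactive for a week triggers an alert. The group wording in the Abstract could be an arm label, since Trial Design and the abbreviation list expand the arms as internet-based or internet-delivered. Zoom is also used around the eligibility interview, so it does not imply groups, and a timed Zoom session could be one-to-one. A session term might also be left to a fuller document.

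Much of this stands. A reader might infer that students are taught in scheduled group sessions and that the false-positive rate therefore more than doubles. The documents do not support that. No session, timetable or group size is described, group delivery is only an inference, and the doubling depends on two assumed quantities. The simulation also assumes that the session effect lasts through every post-baseline visit, which nothing in the article establishes.

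A reader might also cite the ISHE discussion forum as a source of clustering. No subgroups are described for it. If it is arm-wide it is a single cluster, which no model can separate from the treatment. With one therapist described, between-therapist clustering cannot be identified either.

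The contradiction itself remains. The article states both delivery modes, so this is not a matter of condensation. It also names the efficacy model and the sample-size method explicitly, and both fit only one of the two modes.

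**Conclusion.** The point holds as a contradiction with a conditional consequence for the analysis. Under individual delivery the stated ANOVA has no clustering problem and the error rate stays at 5%. Under shared sessions it rises to roughly 6% to 16% for assumed values of 6 to 20 per session and ICC 0.02 to 0.05, with about 10% at 10 per session and ICC 0.05. It more than doubles only when (g − 1) × ICC exceeds about 0.42. Because neither quantity is in the article, no single figure can be claimed.

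**What to change.** Reconcile the Abstract, Trial Design, Study Location and Monitoring of Intervention and Follow-Up Assessment with The Internet Group (CBT-I), and state for each arm whether students share sessions. If delivery is individual, one sentence closes the matter.

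If sessions are shared, record each student's session group. Fit the efficacy model with session group as a random effect nested in arm, or use cluster-robust standard errors with a small-sample correction. State in Sample Size Estimation that the power figure assumes no clustering.

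The cost is one variable and one model term, with wider intervals and fewer degrees of freedom when groups are few. At 10 per session there would be 60 / 10 = 6 groups per arm, leaving 12 − 2 = 10 degrees of freedom between groups; at 20 per session, 3 per arm and 6 − 2 = 4. Results reports T1 and T2 complete for the students enrolled so far, so their session groups may have to be reconstructed, and the article does not say that any session roster is kept. Analysis is scheduled for August 2025, after the last follow-up, so the model can still be settled beforehand.

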### Research Aim and Hypotheses

This study aims to elucidate the effects of improved SQ on executive function. The following hypotheses will be investigated in the trial:

ICBT-I will lead to a significant improvement in SQ compared with the SHE intervention at 1 month (T2), 3 months (T3), and 6 months (T4) postintervention.ICBT-I will lead to a significant improvement in executive functioning compared with the SHE intervention at 1 month (T2), 3 months (T3), and 6 months (T4) postintervention.ICBT-I will lead to a significant improvement in total sleep time (TST), SOL, number of awakenings (NOA), wake time after sleep onset (WASO), and sleep efficiency (SE) compared with the SHE intervention at 1 month (T2), 3 months (T3), and 6 months (T4) postintervention.Dysfunctional beliefs, attitudes about sleep, presleep worry, and sleep hygiene will significantly mediate the between-group differences in study outcomes at 1 month (T2), 3 months (T3), and 6 months (T4) postintervention.

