### Sample Size Estimation

As shown in Figure 3, the sample size for the RCT was calculated using G*Power software (Heinrich-Heine-Universität Düsseldorf), selecting the *F* tests for analysis of variance: repeated measures, within-between interaction. The calculation was based on a precision level of 0.05, a study power of 95%, an effect size of 0.20, and a correlation coefficient of 0.5 among the outcome measures. Therefore, the minimum required sample size for each group is 56. A low effect size of 0.20 was chosen based on previous interventions addressing SQ [33]. After adjusting for a 10% dropout rate, the sample size was increased to 60 medical students per group. Given that this is a 2-arm RCT, a total of 120 medical students will be required to complete the study.

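### Two primary outcomes, each claimed at three time points, share one unadjusted 0.05 level: false-positive risk is about 9–10% on the planned omnibus tests, and effect sizes are tied to significance

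*Protocol article*

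**What the plan says.** - **Primary outcomes.** Abstract, Methods: "The primary outcome is between-group differences in sleep quality and executive function post-baseline". Two outcomes are named, with no order between them and no primary time point.
- **Claims.** Research Aim and Hypotheses predicts a "significant improvement in SQ compared with the SHE intervention at 1 month (T2), 3 months (T3), and 6 months (T4) postintervention", and separately a "significant improvement in executive functioning compared with the SHE intervention at 1 month (T2), 3 months (T3), and 6 months (T4) postintervention".
- **Level.** Sample Size Estimation: "The calculation was based on a precision level of 0.05". The calculation is for one repeated-measures within-between interaction test. Data Analysis gives no test level.
- **Planned test.** Data Analysis plans repeated-measures analysis of variance with treatment and time interaction effects, followed by paired t tests inside each arm. It names no between-arm test at individual time points. Its list of outcomes leaves out executive function, and its time points end at T3.
- **Effect sizes.** Data Analysis: "Significant findings and statistical trends will be further analyzed using Cohen" d, in a form that allows for the correlation between pre- and post-treatment values.

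**The concern.** With two primary outcomes and no stated rule, a reader will take a positive result on either as a positive trial. The nominal 5% then applies to each test and not to the trial's main claim. Because the hypotheses repeat each claim at three follow-ups, the number of chances grows further if those claims are tested one by one.

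The effect-size sentence adds a second problem. If d is worked out for results that are significant or nearly so, the values that appear are selected for being large and tend to overstate the effect. They also describe change within an arm, which is not the between-arm contrast that the hypotheses are about.

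**Working it through.** **The plan's own figure.** The article states no family-wise error rate, so there is none to reproduce. The related figure is the sample size, 56 per group. I used λ = f²·N·m/(1−ρ), df1 = m−1 and df2 = (N−2)(m−1), with f = 0.20, ρ = 0.5, α = 0.05 and power 95%. The number of measurements m is not given in the text. For m = 4, λ at N = 56 is 0.04 × 56 × 4 / 0.5 = 17.92 and power is 95.4%. So I obtain 56 as a total, not per group. That is a separate matter and is used here only to cost the fix.

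**Inputs for the error rate.**
- From the article: two primary outcomes, three claimed time points each, level 0.05, and correlation 0.5, read here as correlation over time.
- Assumed: correlation between the two outcomes, which the article does not give, taken as 0, 0.3 and 0.5; two-sided tests; no true effect on either outcome.

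**Reading A: one omnibus interaction test per outcome, either counts.** This follows Data Analysis, extended to executive function and T4 so that it covers the hypotheses. If independent, 1 − 0.95² = 0.0975. In 20,000 simulated null trials (60 per arm, T0 and T2–T4) the rate was 9.7%, 9.3% and 9.2% for between-outcome correlation 0, 0.3 and 0.5. If between-arm tests at single time points are made only after a significant omnibus test, the rate is 7.4–7.7%.

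**Reading B: six separate between-arm tests, any one counts.** If independent, 1 − 0.95⁶ = 0.265. With time correlation 0.5, simulation of 2,000,000 multivariate normal draws gives 23.5%, 23.0% and 22.0% for between-outcome correlation 0, 0.3 and 0.5. Over time correlations 0.3 to 0.9 and between-outcome correlations 0 to 0.5, the range is 25.4% down to 14.9%.

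**Reading B, false superiority of ICBT-I only.** At time correlation 0.5 this is 11–12%. The matching nominal value for one direction of a two-sided 0.05 test is 2.5%.

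**Reading C: conjunctive success.** Time correlation is 0.5, with errors in either direction. If a hypothesis holds only when all three time points are significant, the rate is about 0.3% per outcome and 0.6% for either outcome. If both outcomes are needed, each at any time point, it is 1.6–3.1%.

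| Decision rule | False-positive risk |
|---|---|
| Either outcome, one omnibus test each | 9–10% |
| Either outcome, time-point tests gated on the omnibus test | 7.4–7.7% |
| Any of six time-point tests, two-sided | 22–23.5% (26.5% if independent) |
| Any of six, false ICBT-I superiority only | 11–12% |
| All three time points on either outcome | 0.6% |
| Both outcomes, each at any time point | 1.6–3.1% |

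**The case against.** A reader might infer that the plan carries a 22–23% false-positive risk because any of six results counts as success. The documents do not support that as a fixed property. Data Analysis plans an omnibus repeated-measures test and names no between-arm test at each time point, and the sample size rests on the same kind of test. The hypotheses join the three time points with *and*, and the Discussion expects improvement in both outcomes, so a conjunctive reading is possible and brings the risk well below 5%. The hypotheses are also directional, so counting results in favour of SHE enlarges the figure. Finally, 0.05 is tied to the sample size alone, and a multiplicity rule may sit in an analysis plan that is not shown.

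A reader might also infer that effect sizes will be reported only when significant. The article says that such results will be further analysed; it does not say that other estimates will be withheld, and it plans descriptive summaries of the outcome measures.

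Most of this stands, and it limits the size of the point. It does not remove it. The analysis closest to the article's own description still gives about twice 5% when either outcome counts. The conjunctive rule is nowhere stated as the rule for success. The omnibus defence is itself incomplete, because the analysis as listed covers neither executive function nor T4. The point rests on what the article fixes, namely two unranked primary outcomes, three claimed time points each, and effect sizes tied to significance, and not on the mere absence of an adjustment.

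**Conclusion.** The point holds in a limited form. If success on either primary outcome counts, the false-positive risk is about 9–10% on one omnibus test per outcome. It rises to about 22–23.5% only if the time-point hypotheses are tested as six separate two-sided between-arm comparisons, with time correlation 0.5 and an assumed between-outcome correlation of 0 to 0.5. Counting errors in either direction, it falls below 5% only under a conjunctive rule that the article does not adopt. Applying 0.05 to each test is an inference from the sample-size section. The effect-size sentence selects on significance and describes within-arm change. How far this would bias reported effects cannot be quantified from the article, and it does not show that between-arm estimates will be withheld. The change should be made before analysis.

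**What to change.** 1. Keep one between-group treatment-by-time test per primary outcome, on the PSQI total and one named dTMT score, over time points that include T4. The dTMT section lists completion time and errors for two parts, so one score has to be named.
2. Control error across the two tests, either by Holm or by testing PSQI first and dTMT only if PSQI is significant. The ordered version fits the trial's rationale that better sleep leads to better executive function.
3. Make between-arm claims at T2, T3 or T4 only for an outcome that passes, and call everything else supportive. This gate protects against error when there is no effect at any time. If the effect is real at one follow-up only, two unadjusted tests at the others could still err with probability up to about 1 − 0.95² = 9.75% if independent. So adjust among the three time points (Holm, for example) if each is to be a confirmatory claim.
4. Replace the significance-conditional d with the between-arm difference, a standardised effect and a 95% CI for every outcome and time point, whatever the p value.
5. Record that the rule was set without reference to the T1 and T2 data. The Results section says these are already collected, and the Blinding section gives the analyst access to all data.

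**Cost.** Mainly wording. Under Holm each outcome loses a little power: with the plan's inputs, four measurements and the same effect-size convention as above, the required total at 0.025 rises from 56 to 64, below the planned 120. Under the ordered version, no confirmatory claim on executive function is possible if PSQI fails.
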